### Recruitment {15}

The enrollment of the target sample size will be ensured by specific strategies based on loyalty. The research team has drawn upon already consolidated collaboration with several schools in the city. Moreover, all students completing all assessments will be awarded books or e-books.

## Assignment of interventions: allocation

### Sequence generation {16a}

After enrollment, the statistician will randomly assign the classes within each school to experimental or control conditions. More specifically, a random sequence of strings (of length equal to the number of school classes) with labels “Experimental” or “Control” will be generated by a computer code, with a ratio of 1:1 (experimental vs. control). The classes will then be linked to the random sequence following their alphabetic order.

### Concealment mechanism {16b}

Allocation concealment will be ensured since the statistician service will not release the randomization code until the classes of students have been recruited into the trial, which takes place after all baseline measurements have been completed.

### Implementation {16c}

The statistics service of IRCCS Fatebenefratelli San Giovanni di Dio will generate the allocation sequence, which will be stored in a digital database protected by passwords on a secure server at the study site. Only the statistician will have access to the list. The PI’s collaborators will be responsible for recruitment and will request the randomization code after the baseline assessment session. Then, the PI will inform the schoolteacher about the final assignment of each class.

## Assignment of interventions: blinding

### Who will be blinded {17a}

Given the nature of the intervention, neither the project psychologists nor the participants could be blinded to the intervention. Outcome assessment will be based on self-report questionnaires, and data analysts will be blinded.

### Procedure for unblinding if needed {17b}

The design is open label with only data analysts being blinded, so unblinding will not occur.

## Data collection and management

### Plans for assessment and the collection of outcomes {18a}

To enhance data validity, assessment sessions will be planned at school for each class of students at baseline, post-intervention, and at 3 and 6 months of follow-up. The researcher will remain available during the sessions to answer students’ questions and to ensure that students complete the questionnaires independently.

### Plans to promote participants’ retention and complete follow-up {18b}

To promote both involvement in the evaluation and to ensure that each participant can complete the entire evaluation, all activities will be planned in agreement with school personnel during the school period. Moreover, one or two teachers will be identified as the contact persons for each class. We did not set criteria to define drop-out; however, we registered attendance at the sessions for each participant. All participants will be invited to complete and follow-up questionnaires independent of attendance.

### Data management and storage {19}

Participants will complete the paper-based battery of questionnaires at school. At the end of the assessment session, the researcher will collect the completed questionnaire and will bring the forms to the IRCCS Istituto Centro San Giovanni di Dio Fatebenefratelli. Data will be registered in a digital database that will be stored at the study site following procedures in line with privacy policies. In particular, after obtaining informed consent, each participant will be associated with an alphanumeric unique code, databases will be stored on a secure server, and they will be protected by passwords. All the material will be stored in a locked archive in areas with limited access. Only authorized research personnel will have access to the database. Quality data checks will be performed after each assessment session by the PI and research personnel to ensure that guidelines for data collection are followed.

### Confidentiality {27}

After obtaining informed consent, each participant will be associated with a unique alphanumeric code. The identification list of subjects will be kept in the investigator’s file and separated from other files. All electronic files will be stored on a secure server and protected by passwords. Only authorized research personnel will have access to the database. The researcher will provide the paper-based battery of questionnaires to each participant corresponding with his/her unique alphanumeric code. The data will be shared only upon reasonable request, to be evaluated by the PI.

### Workflow for collection, laboratory evaluation, and the storage of biological specimens for molecular analysis {33}

After completing the questionnaires, the researcher will explain the procedure to collect salivary samples via OraGene tubes and Salivette, which will be used to measure a panel of inflammatory mediators with Luminex technology. RNA samples from OraGene tubes will be isolated using RNAesy Kits, RNA samples will be processed to obtain a gene expression profile by employing the RNAseq technique on the Illumina platform, and the data will be analyzed to identify peripheral genes associated with ED. Tubes for diurnal cortisol sample collection that will be carried out the next day (morning, afternoon, evening) will also be provided to each individual, and saliva samples will then be analyzed for cortisol levels via ELISA. Information reporting all the detailed steps regarding the exact procedure to gather saliva samples for cortisol measurements will be provided. On this form, there is also a dedicated space that can be used by the students to annotate the exact time of sample collection and any problems that occurred during saliva collection. Salivary samples gathered with both Oragene and Salivette will be stored at − 20 °C until subsequent analysis. The salivary samples will be used only for the purpose reported in this protocol.

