### Strategies to improve adherence to interventions {11c}

All activities of the study will be scheduled during regular school time according to academic planning to facilitate students’ attendance.

The contents of the psychoeducational intervention will be structured. The fidelity to the intervention will be supported by regular meetings of the project team. Team meetings will be scheduled weekly during the pre-study phase and will then be scheduled monthly. For each session of the psychoeducational intervention, the co-leader will fulfill a checklist to register the content of the session and to record students’ attendance.

Adherence to the procedure for salivary sample collection will be promoted by phone alert messages at established hours and by written reminders about the exact procedure.

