## Statistical methods

### Statistical methods for primary and secondary outcomes {20a}

Descriptive statistics (frequencies and percentages for categorical variables, and means and standard deviations for continuous variables) will be evaluated. To compare categorical variables, the chi-squared test will be used. To compare continuous variables between the different groups of interest, *t*-tests, ANOVA, or corresponding non-parametric tests (Mann–Whitney or Kruskal–Wallis) will be performed. Moreover, generalized mixed models will be harnessed to assess the differences in dysfunctional behaviors and emotional regulation skills across time and between groups (including post hoc analyses).

Differences in the levels of the biomarkers will be assessed by using linear and generalized linear models adjusting for potential confounders such as sex. Correlations (Pearson or Spearman) and generalized linear models will be employed to assess the association between the level of emotional dysregulation and other clinical variables and biomarkers.

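### Cortisol sampling as described has no waking time and no day-type rule, so morning values may be confounded by waking schedule; the biomarker model named also does not reflect repeated samples within classes

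*Protocol article*

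**What the plan says.** All references are to the protocol article.

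- **Day.** Section {33}: "Tubes for diurnal cortisol sample collection that will be carried out the next day (morning, afternoon, evening) will also be provided to each individual". The reference point is the questionnaire session, and section {18a} organises sessions by class: "assessment sessions will be planned at school for each class of students at baseline, post-intervention, and at 3 and 6 months of follow-up". Students in a class therefore share a sampling day.
- **Clock.** Section {11c} says that adherence to saliva collection will be "promoted by phone alert messages at established hours and by written reminders about the exact procedure". The hours are not given and no link to waking is stated.
- **What is recorded.** Section {33} describes "a dedicated space that can be used by the students to annotate the exact time of sample collection and any problems that occurred". Waking time is not among the stated items.
- **Instructions.** Section {33} also says: "Information reporting all the detailed steps regarding the exact procedure to gather saliva samples for cortisol measurements will be provided". That student form is not shown.
- **Visits.** Trial design {8} has saliva taken at baseline and after the intervention.
- **Analysis.** Section {20a} assigns biomarkers "linear and generalized linear models adjusting for potential confounders such as sex", and correlations for their association with emotional dysregulation. Generalized mixed models are named there only for dysfunctional behaviours and regulation skills.

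**The concern.** The article treats cortisol as varying over the day: it asks for three samples, and its background section rests on studies of morning cortisol. If the level at a given clock hour also depends on how long the student has been awake (a physiological assumption that the article does not state), two students prompted at the same hour who woke at different times are at different points on their curves. Recorded clock time does not repair this; time since waking is needed.

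Two uses of the data are exposed.

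1. Objectives {7} compares biomarkers between subgroups formed by baseline DERS score. This comparison is not randomised. If late or irregular waking goes with emotional dysregulation, a morning-cortisol difference could partly reflect when students got up.
2. The same section uses post-intervention saliva to study the role of biology in the intervention's effect. If some sessions are followed by a free day and others by a school day, day type becomes a factor shared by a whole class at a visit, and there are only 20 classes.

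The named model adds a separate problem. Samples from one student are correlated, as are students in one class, and a plain linear or generalized linear model does not represent either correlation.

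**Working it through.** The plan gives no figure that depends on cortisol timing. Sample size {14} rests only on the two questionnaire outcomes, so there is nothing to reproduce. The check is a reading of the sections plus two illustrations on assumed values.

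**Reading.** Could another section supply the missing day rule? The nearest is in {11c}: "All activities of the study will be scheduled during regular school time according to academic planning to facilitate students’ attendance". This can govern the session. It cannot literally cover evening samples, and it does not say that the day after a session is a school day. No weekday, school calendar or start time is given.

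**Data structure.** 3 samples × 2 visits = 6 cortisol values per student, in 20 classes of about 22–23 students (section {9}).

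**Illustration 1: waking time.** Assume cortisol declines after its peak at rate s per hour on the log scale, with s between 0.05 and 0.20. Two students sampled at the same clock hour whose waking times differ by h hours then differ by 1 − exp(−s·h).

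- h = 1: 4.9% (s = 0.05), 9.5% (s = 0.10), 18% (s = 0.20).
- h = 2: 9.5%, 18% and 33%.

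The slope is an assumption. The formula holds only if both students are past the peak; a late waker who is still rising or at peak would not follow it.

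**Illustration 2: day type.** Let d be the assumed shift in morning cortisol between free and school days, in within-class SD, and q the assumed share of classes sampled on a free day. Take m = 22 students per class and 10 classes per arm.

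- Induced ICC = q(1−q)d² / (1 + q(1−q)d²).
- Design effect = 1 + (22 − 1) × ICC.
- SD of the chance difference between arms = d × √(2q(1−q)/10), treating classes as independent.
- Nominal standard error = √(2/220) = 0.095 SD.

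Example with d = 0.5 and q = 0.5: q(1−q)d² = 0.0625; ICC = 0.0625/1.0625 = 0.0588; design effect = 1 + 21 × 0.0588 = 2.24; SD of chance difference = 0.5 × √0.05 = 0.112.

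| d (SD) | Design effect, q = 0.1 | Design effect, q = 0.5 | SD of chance arm difference, q = 0.1 to 0.5 |
|---|---|---|---|
| 0.2 | 1.08 | 1.21 | 0.027 to 0.045 |
| 0.5 | 1.46 | 2.24 | 0.067 to 0.112 |
| 0.8 | 2.14 | 3.90 | 0.107 to 0.179 |

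With q = 0 the design effect from this source is 1.00 and the chance difference is 0. Holding day type constant therefore removes this class-level component, but not differences in waking time between students.

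**The case against.** The strongest reply is that much of this may be settled in documents not shown. The detailed student form is where waking instructions or a waking-time line would normally sit. A reader might infer that the trial does not collect waking time; the article supports only that it does not mention it. That part of the objection stands, and the request for a waking-time line is conditional on it.

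A reader might also infer that morning cortisol does shift by class and by visit. The document does not support this either: no session weekdays are given, and if every session precedes a school day there is no shift from day type. Several design features also help:

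- Classes are randomised within school, with an even number per school ({9}, {16a}), so school-wide timetables are shared across arms. Illustration 2 ignores this.
- The code is withheld until baseline measurements are complete ({16b}), so the baseline sampling day cannot depend on arm.
- Sleep quality is collected at baseline ({12}) and could be adjusted for, although it does not give waking time on the sampling day.

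On analysis, sex is given only as an example confounder, and further covariates belong in an analysis plan. The article does not say how the three samples are summarised, so it should not be read as specifying a separate model for each time of day. A single daily summary would remove the within-day repetition. It would still leave two visits per student and students nested in classes, and the article names mixed models for the questionnaire measures but not for biomarkers. That part of the concern survives whatever the student form says.

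Finally, saliva is exploratory and cortisol is not among the outcomes listed in {12}. This limits the scope of the point but does not remove it.

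**Conclusion.** The point holds in a conditional form. As described, sampling is tied to clock hours on the day after a class session, with collection time but no waking time among the stated items and no stated day-type rule. Morning cortisol may therefore be confounded by waking schedule in the baseline comparison by emotional dysregulation. It may also cluster by class and visit if some sampling days are free days.

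The size cannot be derived from the document. It is nil if all sampling days are school days and waking times are similar. Under the assumed slopes, a waking difference of 1 to 2 hours corresponds to about 5–33%; under the assumed day-type shifts, the design effect runs from 1.08 to 3.90. These ranges rest on the assumptions above and are not estimates for this trial.

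The mismatch between the named biomarker model and the nested, repeated data rests on the article's own text. None of this bears on the primary outcomes, the sample size or the efficacy conclusion.

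**What to change.** 1. Add one line for that day's waking time to the saliva form, if it is not already there.
2. Book baseline and post-intervention sessions so that the next day is a school day, with the same day type at both visits and for the experimental and control classes of a school.
3. Analyse log cortisol from all samples in one mixed model with time since waking, a student random intercept and a class random effect, and take the level and the diurnal slope from that model. The class effect is needed because day type and allocation both act at class level.
4. For samples already collected (recruitment began in November 2019), use recorded clock time and the day type reconstructed from session dates. This is a partial repair, because recorded clock time and day type do not give time since waking.

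The cost is one form line, a scheduling rule and model wording. The downside is slightly less freedom in booking sessions and some missing waking times.

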## Statistical methods

### Statistical methods for primary and secondary outcomes {20a}

Descriptive statistics (frequencies and percentages for categorical variables, and means and standard deviations for continuous variables) will be evaluated. To compare categorical variables, the chi-squared test will be used. To compare continuous variables between the different groups of interest, *t*-tests, ANOVA, or corresponding non-parametric tests (Mann–Whitney or Kruskal–Wallis) will be performed. Moreover, generalized mixed models will be harnessed to assess the differences in dysfunctional behaviors and emotional regulation skills across time and between groups (including post hoc analyses).

Differences in the levels of the biomarkers will be assessed by using linear and generalized linear models adjusting for potential confounders such as sex. Correlations (Pearson or Spearman) and generalized linear models will be employed to assess the association between the level of emotional dysregulation and other clinical variables and biomarkers.

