### Objectives {7}

The aim of the present study is twofold. The first is to evaluate the impact of a school-based intervention focused on emotional regulation strategies in a sample of adolescent students. The primary outcome will be changes in the frequency of use of emotional regulation skills and changes in the frequency of impulsive behaviors. Our hypothesis is that (1) at the end of intervention, the students who received the intervention will report a reduction in the frequency of impulsive behaviors compared to baseline, whereas we expect no differences in the group of adolescents who will not receive the intervention; (2) at the end of intervention, the students will report an increase in the use of emotional regulation skills compared to baseline, while we expect no differences in the control group; and (3) these changes will be maintained at 3 and 6 months of follow-up.

The second aim was to assess the association between biological features and ED in adolescent students. Specifically, we will compare several biomarkers related to stress response and inflammation in subgroups of students with different levels of ED assessed with the Difficulties in Emotion Regulation Scale (DERS) [4] measured at baseline. Moreover, the repeated collection of salivary samples post-intervention will allow us to evaluate the role of these biological features in the interventions’ effects on the behavioral variables described above (i.e., impulsive behaviors and use of skills).

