### Trial design {8}

This is an interventional, parallel assignment, two-arm, cluster randomized trial. The classes of students will be randomized into a psychoeducational intervention (experimental group) or control condition (control group). All participants will be assessed at baseline, post-intervention, and at the 3- and 6-month follow-up points by using self-report questionnaires. In addition, salivary samples will be collected at baseline and post-intervention. Details on the timeline and assessments are reported in Table 1.

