## Methods: participants, interventions, and outcomes

### Study setting {9}

A total of 20 school classes will be recruited among the high schools of Brescia (Northern Italy), for a total of approximately 440–460 students (considering approximately 22–23 students per school class) attending several high schools in the city. Each school will enroll an even number of classes to be randomized to the experimental or control conditions.

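### The two-sample tests named for comparing groups treat students as independent although whole classes are randomised, so arm-comparison p-values are too small if the class intraclass correlation is above zero

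*Protocol article*

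**What the plan says.** **Design.** Trial design {8} states: "This is an interventional, parallel assignment, two-arm, cluster randomized trial". Study setting {9} adds: "A total of 20 school classes will be recruited among the high schools of Brescia", "considering approximately 22–23 students per school class". Under Sequence generation {16a}, "the statistician will randomly assign the classes within each school to experimental or control conditions", in a 1:1 ratio.

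**Primary outcomes.** Under Outcomes {12}, both primary measures (DBT-WCCL and CIB) are analysed as a between-group difference in the proportion of students who moved at least one category in the favourable direction from baseline to post-intervention. Secondary outcomes are differences in mean score between baseline and post-intervention.

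**Analysis.** Statistical methods {20a} says: "To compare categorical variables, the chi-squared test will be used". Continuous variables get t-tests, ANOVA or their rank-based counterparts. A further sentence adds that "generalized mixed models will be harnessed to assess the differences in dysfunctional behaviors and emotional regulation skills across time and between groups". Biomarker levels are compared with linear or generalised linear models adjusted for confounders such as sex. No class or school term is named in that section, no analysis is called primary, and Sample size {14} gives neither an ICC nor a design effect.

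**The concern.** The article calls the trial cluster randomised and then names tests whose standard errors are right only if students were randomised and respond independently. Classmates share a room, teachers and peers, and in the experimental arm they also share group sessions, class exercises and a classroom poster, so a positive class correlation is plausible. If it exists, a chi-squared or t-test comparing the arms counts some of the class-to-class variation as evidence about the intervention. A null intervention would then be declared effective more often than the stated 5%, for the primary and the secondary outcomes alike.

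**Working it through.** **1. Inputs from the article.** 20 classes at 1:1 give 10 per arm. About 22 students are enrolled per class. The sample-size section needs 340 analysable students, and 340/20 = 17 per class. Its drop-out step reproduces: 170/0.8 = 212.5, rounded up to 213 per group, or 426. Nominal two-sided alpha is 0.05.

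**2. Assumption.** The article gives no ICC. I use 0.01 to 0.10.

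**3. Formula.** With m students per class, the true variance of the arm contrast is the independent-student variance multiplied by DE = 1 + (m − 1) × ICC. The actual type I error of the unadjusted test is 2 × [1 − Φ(1.96/√DE)].

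Example for ICC 0.05:
- m = 17: DE = 1 + 16 × 0.05 = 1.80, 1.96/√1.80 = 1.46, error 0.144.
- m = 22: DE = 1 + 21 × 0.05 = 2.05, 1.96/√2.05 = 1.37, error 0.171.

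| ICC (assumed) | DE, m = 17 | Error, m = 17 | DE, m = 22 | Error, m = 22 |
|---|---|---|---|---|
| 0.01 | 1.16 | 6.9% | 1.21 | 7.5% |
| 0.02 | 1.32 | 8.8% | 1.42 | 10.0% |
| 0.05 | 1.80 | 14.4% | 2.05 | 17.1% |
| 0.10 | 2.60 | 22.4% | 3.10 | 26.6% |

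**4. Chi-squared by simulation, ICC on the binary outcome scale.** Beta-binomial data, no true effect, 10 classes per arm, an assumed 30% improved, 20,000 runs per setting. For ICC 0.01/0.02/0.05/0.10, chi-squared rejects 6.9/8.6/14.6/22.8% (m = 17) and 7.4/10.1/17.1/26.4% (m = 22). A t-test on class-level results holds 4.8–5.2%.

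**5. Randomisation within schools, ICC on a latent continuous scale.** 20 classes of 17, five schools (the number of schools is also an assumption), 3,000 runs, so the Monte Carlo standard error near 5% is √(0.05 × 0.95/3000) ≈ 0.4 percentage points.

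| Class ICC | t-test on students | Chi-squared, 13% outcome | t-test on class means |
|---|---|---|---|
| 0 | 4.9% | 5.2% | 4.7% |
| 0.02 | 8.9% | 6.9% | 5.3% |
| 0.05 | 14.7% | 8.7% | 5.1% |
| 0.10 | 22.8% | 12.3% | 4.2% |

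The chi-squared figures are lower than in step 4 because a given latent ICC becomes a smaller ICC once the outcome is dichotomised at 13%.

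**6. School effect alone.** With a school ICC of 0.05 and no class effect, the student-level t-test rejects 4.9% (five schools) or 4.2% (ten schools). With school effects present, the class-mean t-test that leaves school out rejects only 1.1–2.4%. Leaving out the stratum therefore makes a test conservative or imprecise. It does not make p-values too small.

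**The case against.** **The mixed models may already solve it.** They cover both primary domains and compare groups, and an article may leave random effects and degrees of freedom to a fuller plan. This stands in part: the wording does not exclude a class effect, so it would be wrong to say that every efficacy test is inflated. It does not settle the point. The sentence comes as an addition to the chi-squared and two-sample tests, nothing ranks it above them, and it leaves out problem-solving, emotional dysregulation as measured by the DERS, depression, anxiety and impulsivity. The difficulty is that tests unsuited to the design are named, which is different from detail being absent.

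**Not every simple test is an arm comparison.** True. ANOVA and Kruskal–Wallis may be meant for the subgroups by level of emotional dysregulation. The baseline biomarker comparisons across those subgroups are observational, so the argument from cluster randomisation does not carry over to them.

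**Stronger readings that the article does not support.**
- A reader might infer that leaving out the school strata also shrinks p-values. Step 6 shows that it does not.
- A reader might infer that baseline is ignored. It enters through the definition of improvement, through the change-based secondary outcomes and through time in the mixed model. Omitting it as a covariate costs precision and does not raise the false-positive rate of a randomised comparison.
- Objectives {7} says of the controls "whereas we expect no differences in the group of adolescents who will not receive the intervention", and a reader might infer a plan to test each arm separately. That passage states expectations. The efficacy criteria under Outcomes {12} are between-arm for both primary measures.

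**Conclusion.** The point holds for class clustering. The two-sample tests named in {20a} do not match the randomisation described in {8}, {9} and {16a}, and the one model that could account for class is neither specified to do so nor made primary. If the class ICC is above zero, arm-comparison p-values from these tests are too small. The size depends on assumed ICCs. For 0.01–0.10 on the outcome scale, actual error at nominal 5% is about 7–22% with 17 analysed per class and 7–27% with 22. For a 13% binary outcome with a latent-scale ICC of 0.02–0.10 it is about 7–12%. At an ICC of exactly zero there is no inflation. The 30% and 13% outcome rates and the number of schools used in the simulations are also assumptions. This needs correcting before analysis, since it governs the validity of the primary result.

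**What to change.** In Statistical methods {20a}:

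1. For each primary outcome as defined (binary improvement, compared between arms at post-intervention), name as the primary efficacy analysis either a generalised mixed model with a class random effect or a class-level analysis. State a small-sample correction for 20 clusters. A class-level t-test has at most 20 − 2 = 18 degrees of freedom, fewer with school terms.
2. Use the same class-accounting approach for the secondary outcomes and for post-intervention biomarker comparisons between arms.
3. Restrict unadjusted chi-squared, t and rank tests to description.
4. As a separate gain in precision, include school as the randomisation stratum and, for continuous outcomes, the baseline score as a covariate.

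The cost is a few sentences and modest additional code. No data collection changes. Confidence intervals will be wider than the unadjusted ones, and they will be valid for the design.
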